### Adverse events

2.10

AEs (serious and nonserious AEs), adverse drug reaction (ADR), and unexpected ADR will be defined accordingly to “ICH Guidance for Clinical Safety Data Management: Definitions and Standards for Expedited Reporting.”

All AE occurring between the first study-related procedure and the last study-related procedure will be reported. Those meeting the definition of serious AE (SAE) will be reported in an ad hoc SAE Form; they will be reported to coordinating center within 24 hours.

The following AEs have been reported during the use of Rapamycin, mainly in transplanted patients and in association with other drugs (Table 3).

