**Table 3 T3:**
[figure not shown]
Adverse reactions reported with Rapamycin use.

Investigators must adhere to specific safety rules established for the following toxicities, regardless of the causal relationship to study treatment: respiratory toxicity; metabolic toxicity; cardiovascular toxicity; gastrointestinal toxicity; hematological toxicity; genitourinary toxicity; renal toxicity; reproductive system and pregnancy; hypersensitivity Reactions; skin toxicity; carcinogenicity; and increased susceptibility to infection.

The risk management plan for AEs not described above and suspected to be related to study treatment is as follows:

At the first occurrence of moderate AE (grade 2): study treatment will be interrupted until AEs has returned to baseline value or mild intensity, then resumed at the same dose level according to local investigator judgment.If the same moderate AE reoccurs, study treatment will be interrupted.In case of severe AE (grade 3), study treatment will be interrupted until AE has returned to baseline level or mild intensity, then resumed with a dose reduction (1 step).In case of life-threatening or disabling AE (grade 4), study treatment must be definitely discontinued.

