### Safety assessment

2.11

Safety will be assessed on the following variables: occurrence of AEs and per-treatment arising changes in physical examination, vital signs (blood pressure, pulse rate, and body temperature), body weight, and clinical laboratory tests (biochemistry, hematology). MedDRA dictionary is going to be used for reporting.

All AEs will be actively collected at each visit, from spontaneous declarations of the patient as well as from oral inquiry and clinical examination. All concomitant medications and/or therapies should be documented in the patient file and reported in the electronic Case Report Form (eCRF).

The following biological parameters will be assessed according to study flow chart (Table 2)—hematology: count of red blood cells, hemoglobin, hematocrit, total white blood cells count, platelet count, and a differential count including neutrophils, lymphocytes, monocytes, eosinophils, and basophils; biochemistry includes urea, creatinine, albumin, protein electrophoresis, AST (SGOT), ALT (SGPT), gamma GT, LDH, cholesterol, triglycerides, sodium, potassium, glucose; screening for infectious diseases including HIV, hepatitis B, hepatitis C, and tuberculosis. An electrocardiogram and chest X-ray (only posterior–anterior view) will be performed at screening. At treatment end (week 18) these exams can be repeated based on clinical opinion of the caring neurologist.

A physical examination including vital signs (systolic and diastolic arterial pressure, heart rate) and body weight will be performed according to the Visit Schedule (Table 2). Check for adequate contraception will be performed at every visit. Respiratory function will be monitored with FVC.

Stopping rules for single patient have been established for each AE.

Stopping rule for the RCT has been established too. We will consider the following list of toxicities as acceptable: peripheral edema, hypertriglyceridemia, hypercholesterolemia, constipation, arthralgia, thrombocytopenia (not severe), anemia (not severe), leukopenia (not severe), rash, hypertension, increased creatinine, abdominal pain, diarrhoea, headache, fever, urinary tract infection, nausea, lymphocele, tachycardia, stomatitis, abnormal healing, increased lactic dehydrogenase, hypokalemia (not severe), diabetes mellitus, epistaxis, ovarian cysts, and menstrual disorders (amenorrhea and menorrhagia).

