The study will be stopped by the DSMB in case of >30% of patients experience one of the following side effects: pneumonia, sepsis, venous thromboembolism, thrombotic thrombocytopenic purpura/hemolytic uremic syndrome, severe leukopenia or anemia or thrombocytopenia, bone necrosis, melanoma, and skin cancer. In other words, the trial will be stopped if any of the abovementioned SAEs occurs in ≥6 patients.

As for mild and moderate AEs, the DSMB will be notified if 50% of all subjects report a given mild or moderate severity adverse effect.

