### Data recording and data monitoring

2.12

The investigators will collect data by entering them directly into the trial database, through electronic case report forms ad hoc developed. At the end of the RCT, database will be locked and an expert Statistician will check the database and extract all data for statistical analyses.

The study will be monitored by a certified contract research organization (CRO). A monitor will be in charge of safety data downloads and review on monthly basis (AEs), laboratory data downloads, including Rapamycin levels on fortnightly basis. Data safety and monitoring board (DSMB) meetings will be scheduled (starting when the first 10 patients enrolled would have been treated for 3 months and then when 50% of patients would have completed at least week 8 of treatment and subsequently after every 3 months). All SAEs will be reviewed by the DSMB. As for mild and moderate AEs, the DSMB will be notified if 50% of all subjects report a given mild or moderate severity adverse effect.

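### Minor: the 50% DSMB notice counts only mild or moderate reports, so severe-only, non-serious cases drop out of the count and can delay it

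*Protocol article*

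**What the plan says.** The notice appears twice. Section 2.11 (Safety assessment), straight after the trial stopping rule, says that "the DSMB will be notified if 50% of all subjects report a given mild or moderate severity adverse effect". Section 2.12 (Data recording and data monitoring) repeats it beside the route for serious events: "All SAEs will be reviewed by the DSMB. As for mild and moderate AEs, the DSMB will be notified if 50% of all subjects".

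Three other statements decide who is counted or otherwise brought to the DSMB:

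- Section 2.10 (Adverse events) makes seriousness the criterion for the SAE form: "Those meeting the definition of serious AE (SAE) will be reported in an ad hoc SAE Form".
- The management rules after Table 3 treat severe as its own grade, above moderate (grade 2) and below life-threatening or disabling (grade 4): "In case of severe AE (grade 3), study treatment will be interrupted until AE has returned to baseline level or mild intensity".
- The trial stopping rule in section 2.11 names severe forms for three blood-count effects only; its list ends "severe leukopenia or anemia or thrombocytopenia, bone necrosis, melanoma, and skin cancer".

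Several safeguards do not depend on the notice. Section 2.11 states "Stopping rules for single patient have been established for each AE". Section 2.12 provides monthly review of adverse events, "laboratory data downloads, including Rapamycin levels on fortnightly basis", and DSMB meetings. The first meeting comes when the first 10 patients have had 3 months of treatment, the next when half the patients have completed week 8, and later ones every 3 months.

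**The concern.** A frequency alert should be at least as easy to trigger when the same effect occurs at a worse grade. This one becomes harder to trigger: if one subject's only episode is severe rather than moderate, that subject leaves the numerator.

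The lost subjects are a narrow group. Their only report of the effect is grade 3, it does not meet the definition of serious, and the effect is not on the stop list. Severe but non-serious stomatitis, diarrhoea or rash would fit. Such a case starts the patient-level rules but adds nothing to the 50% count and does not reach the DSMB as an SAE.

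What is at stake is when the DSMB learns that an effect has become common. The notice is the numeric alert that works between meetings. Meetings settle to a 3-month interval while treatment lasts 18 weeks, so a missed notice could cost a noticeable part of the treatment period before the pooled frequency is seen.

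**Working it through.** **Inputs.** Subjects: 3 arms × 21 = 63 (section 2.4). Notice: 50% of all subjects, mild or moderate reports only (sections 2.11 and 2.12). The article gives no count for the threshold and no severe-only share. The shares and incidences below are therefore assumptions, shown over a range.

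**Threshold.** 0.5 × 63 = 31.5, so K = 32 subjects.

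**Subjects who must be affected before the notice is due.** Let p be the share of affected subjects whose only episode is severe and non-serious, and T the number affected at any grade. As written, the notice needs T × (1 − p) ≥ 32, so T is 32 / (1 − p), rounded up.

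| p (assumed) | 32 / (1 − p) | T needed | T needed if any severity counts |
|---|---|---|---|
| 0 | 32.0 | 32 | 32 |
| 0.05 | 33.7 | 34 | 32 |
| 0.10 | 35.6 | 36 | 32 |
| 0.20 | 40.0 | 40 | 32 |
| 0.30 | 45.7 | 46 | 32 |

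**Worked case.** With 31 mild or moderate and 9 severe-only subjects, 31 + 9 = 40 are affected, and 40/63 = 63%. As written, 31 < 32 and no notice is due. Counting any severity, 40 ≥ 32 and it is due. If just one of the 9 also had a milder report, the count would be 32 and the notice would be due as written.

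**If all subjects means those enrolled so far.** With 30 enrolled, K = 15. With 14 mild or moderate plus 4 severe-only, 18 of 30 (60%) are affected. As written, 14 < 15 and no notice is due; counting any severity, 18 ≥ 15 and it is due. The direction is the same.

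**Chance of reaching the threshold.** Suppose each of the 63 subjects independently has the effect with the same probability π. The number counted is then binomial with n = 63 and probability π × (1 − p), and the table gives P(count ≥ 32).

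| π (assumed) | p = 0, or any severity counted | p = 0.10 | p = 0.20 | p = 0.30 |
|---|---|---|---|---|
| 0.50 | 0.500 | 0.212 | 0.054 | 0.007 |
| 0.60 | 0.946 | 0.738 | 0.375 | 0.100 |
| 0.70 | 1.000 | 0.982 | 0.831 | 0.437 |

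One common π for placebo and rapamycin is a simplification. The table shows direction and sensitivity; it is not a forecast.

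**Limit of any rewording.** With 20 severe cases among the 42 rapamycin subjects and none on placebo, 20 < 32, so no notice is due under either wording.

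**The case against.** The strongest reply is that the authors meant two tiers: worse events reach the DSMB one by one, and lesser events reach it on a 50% count. The text lends this some support. Section 2.11 lists severe blood-count effects and then refers to everything on that list as SAEs, and both sections move directly from SAEs to mild and moderate events. On that reading a severe case gets more DSMB attention, not less. This stands as a plausible account of intent. It does not settle the wording, because the label covers only the listed events. Sections 2.10 and 2.12 send the DSMB serious events, and nothing there brings a severe, non-serious case of an unlisted effect to it individually.

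A second reply is that the scenario is remote. About half of all subjects, placebo included, must share one effect, and enough of them must never be recorded with it at a milder grade. Events are collected at every visit, and under the general management rule a severe event must subside to baseline or mild intensity before treatment resumes, so a milder report may often exist. This stands, and it is why the point is minor.

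A third reply is that a journal article condenses a fuller protocol, where escalation and counting rules may be set out. That disposes of complaints about missing detail. It does not dispose of a rule that is printed twice and moves the wrong way with severity.

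**Conclusion.** The point holds as a minor defect of wording. As written, severe-only, non-serious cases of effects outside the stop list are not counted, and a worse grade mix can delay or prevent the notice. At assumed severe-only shares of 5% to 30%, the number who must be affected rises from 32 to between 34 and 46 of 63. At a share of zero nothing changes. The result rests on a literal reading of the sentence, on severity and seriousness being separate, and on a severe-only share that the article does not give.

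Two stronger readings should be resisted. A reader might infer that severe non-serious toxicity escapes oversight or leaves patients unprotected. The article does not support that: grade-based interruption and dose reduction, single-patient stopping rules, monthly adverse event review, scheduled DSMB meetings and the trial stopping rule all operate without the notice. A reader might also infer a gap for severe hypokalemia, because it is acceptable only when not severe and is absent from the stop list. The two lists need not be complements, section 2.10 refers to specific rules for metabolic toxicity, and a condensed article may leave the detail elsewhere.

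The primary analysis is not affected.

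**What to change.** In sections 2.11 and 2.12, replace the mild-or-moderate limit in the notice, including the opening words that confine it to those grades, with *a given adverse effect of any severity*. Keep the 50% threshold and add that each subject counts once per effect. This also settles how a subject with both a mild and a severe episode is counted.

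The cost is one sentence in two places. Severity is already graded under section 2.10, so no new data are needed. The downside is possibly a few more notices to the DSMB. The change does not create an alert for severe events affecting fewer than half of the subjects.

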### Data recording and data monitoring

2.12

The investigators will collect data by entering them directly into the trial database, through electronic case report forms ad hoc developed. At the end of the RCT, database will be locked and an expert Statistician will check the database and extract all data for statistical analyses.

The study will be monitored by a certified contract research organization (CRO). A monitor will be in charge of safety data downloads and review on monthly basis (AEs), laboratory data downloads, including Rapamycin levels on fortnightly basis. Data safety and monitoring board (DSMB) meetings will be scheduled (starting when the first 10 patients enrolled would have been treated for 3 months and then when 50% of patients would have completed at least week 8 of treatment and subsequently after every 3 months). All SAEs will be reviewed by the DSMB. As for mild and moderate AEs, the DSMB will be notified if 50% of all subjects report a given mild or moderate severity adverse effect.

### Sample size calculation

2.13

The sample size has been estimated considering as the primary outcome measure the proportion of positive response (Tregs number increase) at treatment end (18 weeks) in patients treated with Rapamycin versus placebo.

ALS patients have a slight reduction of Treg% (mean±SD: 2.1 ± 0.7) with respect to healthy controls (2.6 ± 0.6) (Treg% calculated on total lymphocytes; normal values of total lymphocytes: 1000–4500/μL; normal values of total Treg: 71.5 ± 17/μL).^[22]^

Slowly progressive ALS patients have a number of Tregs that is equal to healthy controls, whereas fast progressors have 31% fewer Tregs than slowly progressing patients, and Treg % is inversely correlated with the rate of disease progression.^[8]^ These data indicate that ALS patients have 60 ± 17 Treg/μL (fast progressors: 49.3 Treg/μL; slow progressors: 71.5 Treg/μL). As a result, a “positive response” can be considered an increase of the proportion of Tregs by ≥30%. The null hypothesis is that Rapamycin does not increase significantly the proportion of positive responses in treated patients at 18 weeks compared with their baseline stage and to placebo group. The alternative hypothesis is that Rapamycin determines a proportion of positive responses in ≥50% of treated patients compared with a maximum 5% of patients in the placebo group. The study has been designed to reject the null hypothesis with an alpha error of 0.025 (to take into account a multiple comparison with a control arm) and a power of 0.80. For this purpose, a sample of 54 patients randomized in 3 treatment arms would be needed. Considering an average drop out of 15% then a recruitment of 63 patients will be necessary.

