### Objectives

2.1

The primary objective is to assess whether different Rapamycin doses increase Treg number in ALS patients compared with the control arm.

Secondary objectives include the following:

1.*Assessment of Rapamycin safety and tolerability in a cohort of ALS patients*: occurrence of adverse events (AEs), changes on clinical examination including vital signs and weight, and laboratory examinations (biochemistry, hematology and urinalysis) will be registered throughout the entire study duration.2.*Biological assessment*: To analyze Rapamycin efficacy in inhibiting MTOR pathway, by quantifying the phosphorylation of the S6 ribosomal protein (S6RP) comparing baseline and weeks 8, 18 (treatment end), 30, and 54 between Rapamycin arms and placebo arm. To identify changes in activation and homing capabilities of different T, B, NK cell subpopulations comparing baseline and weeks 8, 18 (treatment end), 30, and 54 between Rapamycin arms and placebo arm. To study Rapamycin effects on different biomarkers (including peripheral and CSF biomarkers, that is, creatinine and albumin, CK, vitamin D, plasma/CSF neurofilament heavy/light chain protein) comparing baseline and week 8, 18 (treatment end), 30, and 54 between Rapamycin arms and placebo arm. To identify Rapamycin-induced changes in inflammatory status, by the molecular analysis of the inflammasome system baseline and week 8, 18 (treatment end), 30, and 54 between Rapamycin arms and placebo arm. To assess Rapamycin capacity to pass through blood–brain barrier (BBB).3.*Clinical assessment*: to assess changes in Amyotrophic Lateral Sclerosis Functional Rating Scale (ALSFRS)-Revised from baseline to weeks 4, 8, 12, 18, 30, 42, and 54 in placebo and treatment arms; overall survival from randomization to date of documented death or tracheostomy; survival rate at weeks 18, 30, 42, and 54; forced vital capacity (FVC) score from baseline to weeks 4, 8, 12, 18, 30, 42, and 54.4.Quality of life assessment: ALSAQ-40 from baseline to weeks 8, 18, 30, and 54 in treatment and placebo arms.

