### Outcomes

2.9

The primary outcome is represented by the change from baseline to week 18 in Treg number in ALS patients treated with Rapamycin compared with the control arm.

Secondary outcomes are as follows:

1.*Safety*: Occurrence of AEs and per-treatment arising changes in physical examination, vital signs (blood pressure, pulse rate, and body temperature), body weight, and clinical laboratory tests (biochemistry, hematology). MedDRA dictionary is going to be used for reporting.2.*Rapamycin levels in CSF* at week 18 (high-performance liquid chromatography (HPLC) with mass spectrometry (MS) (LC–MS/MS).3.Change from baseline to each time point (weeks 8, 18, 30, and 54) of the phosphorylation of the S6 ribosomal protein *(S6RP)* comparing Rapamycin arms and placebo arm.4.Change from baseline to each time point (week 8, 18, 30, and 54) of the activation and homing capabilities of different *T, B, NK cell subpopulations* comparing Rapamycin arms and placebo arm.5.Changes from baseline to each time point (weeks 8, 18, 30, and 54) in different *biomarkers* (including peripheral and CSF biomarkers that is, creatinine and albumin, CK, vitamin D, plasma/CSF neurofilament heavy/light chain protein) comparing Rapamycin arms and placebo arm.6.Changes from baseline to each time point (weeks 8, 18, 30, and 54) in *inflammatory status (molecular analysis of the inflammasome system)* comparing Rapamycin arms and placebo arm.7.Change from baseline to each time point (weeks 4, 8, 12, 18, 30, 42, and 54) of *ALSFRS-R.*8.*Survival* defined as the time from randomization to the date of documented death or tracheotomy.9.Survival rate at weeks 18, 36, and 54.10.*Change of FVC* from baseline to each time point (weeks 4, 8, 12, 18, 30, 42, and 54).11.Absolute and relative change from baseline in *ALSAQ-40* (Amyotrophic Lateral Sclerosis Specific Assessment Questionnaire at weeks 4, 8, 12, 18, 30, 42, and 54).

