### Statistical analyses

2.14

Separate analyses will be performed in

1.all randomized subjects receiving ≥1 dose of study medication (intention-to-treat population);2.all randomized subjects excluding protocol deviations (per protocol, PP population).

Descriptive statistics will be performed comparing the 2 groups of Rapamycin treatment and placebo. Continuous variables will be described using mean and standard deviation or median and interquartile range; categorical variables will be described as counts and percentages.

Safety analysis will be performed in all subjects receiving ≥1 dose of the experimental drug. All AEs, SAEs, and AEs leading to treatment discontinuation will be recorded according to ICH Guidelines, listed, and compared in the treatment arms at any follow-up visit and at the end of the study.

Differences in tracheostomy-free survival (Kaplan–Meier method) between the treated groups and placebo group will be compared using the log-rank test. Cox's proportional hazard model would be used to adjust for any possible unbalanced prognostic factors. Statistical significance will be set at .05 level for a 2-tailed test. Missing data will be handled using the last observation carried forward.

Immune response to Rapamycin will be analyzed as the difference in positive response to Rapamycin (mean Tregs increase >30%) between the placebo group and the Rapamycin groups. This will be calculated with the use of Treg data obtained at baseline and at week 18.

We will compare the mean values of S6RP phosphorylation, of different T, B, NK cell subpopulations, of biomarkers, inflammasome, cytokines, comparing baseline and treatment end (18 weeks) between Rapamycin and placebo arm. Mean differences in plasma concentrations from baseline to week 18 in the 2 treatment arms will be calculated and compared using *t* test or Wilcoxon–Mann–Whitney test.

The mean change over time for the same variables as above will be assessed using repeated measures ANOVA, with treatment as between-subjects factor and time as within-subjects factor. Different models will be used, each with a different biomarker of activity as the dependent variable. Models will be adjusted for any unbalanced distribution of the main prognostic factors (e.g., age) between the 2 treatment arms.

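### The primary responder is stated on two scales, Treg number and Treg proportion, which agree only if the lymphocyte count is stable

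*Protocol article*

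**What the plan says.** Three places in the protocol article put the primary variable on the scale of number:

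- 2.1 Objectives asks "whether different Rapamycin doses increase Treg number in ALS patients compared with the control arm".
- 2.9 Outcomes makes the primary outcome the "change from baseline to week 18 in Treg number in ALS patients treated with Rapamycin compared with the control arm".
- 2.13 Sample size calculation opens by naming the outcome as "the proportion of positive response (Tregs number increase) at treatment end (18 weeks").

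Later in 2.13 the scale changes: a positive response "can be considered an increase of the proportion of Tregs by ≥30" per cent. The reference data in the same section are given as "Treg% calculated on total lymphocytes; normal values of total lymphocytes: 1000–4500/μL", alongside counts per µL.

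2.14 Statistical analyses describes the comparison as the difference in "positive response to Rapamycin (mean Tregs increase >30" per cent, using Treg data at baseline and week 18. It names neither count nor percentage, and its threshold is strict where that of 2.13 is not.

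On the denominator, 2.11 Safety assessment includes "leukopenia (not severe") in its list of acceptable toxicities, and the Discussion describes Rapamycin as immunosuppressive.

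**The concern.** The Treg count is the Treg fraction multiplied by the lymphocyte count. A 30% rise in one equals a 30% rise in the other only when lymphocytes do not change. The only responder definition that names a scale uses the proportion, while the objective and outcome that it is meant to serve use the number.

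Two things are at stake. First, the text lets either scale be chosen after the data are seen, and that choice decides who is a primary responder. Second, if the proportion is used and the drug lowers other lymphocytes more than Tregs, patients can meet the rule with no more Tregs than at baseline. A drug effect on the denominator would arise in the active arms only, so neither the placebo arm nor blinding would remove it.

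**Working it through.** **1. The plan's own figure.** Inputs from 2.13: response 50% versus 5%, alpha 0.025 per comparison with control, power 0.80. Sidedness is not stated there; two-sided is taken here. The pooled-variance formula for two proportions, without continuity correction, has mean proportion 0.275 and gives

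n = [2.241 × √(2 × 0.275 × 0.725) + 0.842 × √(0.25 + 0.0475)]² / 0.45² = 17.4, so 18 per arm and 54 in three arms.

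For dropout, 54 × 1.15 = 62.1 and 54/0.85 = 63.5, so the stated 63 is close on either convention. The sample size rests on assumed response rates, not on a measured SD, and does not depend on which scale was meant.

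**2. The identity.** Count ratio = Treg% ratio × lymphocyte ratio. With an unchanged count, Treg% rises by 30% when the lymphocyte ratio is 1/1.3 = 0.769, a fall of 23.1%. This needs no distributional assumption.

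On the ALS averages in 2.13 (2.1% and 60/µL), implied lymphocytes are 60/0.021 ≈ 2,857/µL. A fall to 2,857/1.3 ≈ 2,198/µL moves Treg% from 2.1 to 2.73 with Tregs still at 60/µL. A responder defined on count would need 60 × 1.3 = 78/µL.

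**3. How far the scales separate.** If Treg% rises by exactly 30%:

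| Lymphocyte fall | Count ratio (1.3 × lymphocyte ratio) |
|---|---|
| 10% | 1.17 |
| 20% | 1.04 |
| 23.1% | 1.00 |
| 30% | 0.91 |

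**4. Illustration only.** The protocol gives no SD of within-patient change and no size of lymphocyte fall. Assume that the within-patient Treg% ratio is log-normal, that the Treg count does not change on average, that every treated patient has the same proportional lymphocyte fall d, and that the log-SD is set so that the 5% placebo ceiling in 2.13 is met exactly: ln(1.3)/1.645 = 0.16. Then

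P(responder) = 1 − Φ([ln 1.3 + ln(1 − d)] / 0.16).

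| Assumed fall d | Responders, no mean change in count |
|---|---|
| 0% | 5% |
| 15% | 27% |
| 20% | 40% |
| 23.1% | 50% |
| 25% | 56% |

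Under these assumptions, a fall of about 23% alone would reproduce the planned 50% versus 5%. The figures move with the SD: setting it from a 1% placebo rate (log-SD 0.113) gives 19% in place of 27% at a 15% fall, and 36% in place of 40% at a 20% fall.

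**5. Which scale the threshold came from.** The healthy-control figures look like a conversion at a fixed lymphocyte count: 71.5/0.026 = 2,750/µL, the midpoint of 1,000 and 4,500, and 0.6% × 2,750 = 16.5, close to the quoted 17. The ALS figures do not follow that conversion: 2.1% × 2,750 = 57.8, not 60, and 0.7% × 2,750 = 19.3, not 17. They follow from counts: 71.5 × 0.69 = 49.3, and (49.3 + 71.5)/2 = 60.4. The 30% threshold follows directly on the statement that fast progressors have 31% fewer Tregs. Its origin therefore points to counts, while its wording says proportion.

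**The case against.** The strongest reply is that proportion is loose wording. It appears once as the responder scale. The abstract, 2.1, 2.9 and the opening of 2.13 say number, 2.14 does not say proportion, and the threshold seems to have been derived from counts (step 5). This stands as a reason not to assert that the trial will be analysed on Treg%. It does not remove the contradiction, because no passage resolves it and the phrase in question is the responder definition itself.

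A reader might infer that the drug will lower lymphocytes and so produce false responders. The document does not support that. It lists non-severe leukopenia as acceptable, which is not a forecast; leukopenia is not lymphopenia; and 2.10 says that the reported adverse events came mainly from transplanted patients and in association with other drugs. Nor must any bias favour the drug: if Tregs and other lymphocytes fall together, Treg% does not move. The reference to total lymphocytes describes published reference data, so even the denominator of the trial's own rule is an inference. All of this stands.

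The percentage also has a rationale in the protocol: the Introduction, 2.13 and the Discussion link blood Treg percentage with progression. That is a good reason to report it, but not to use it silently for an objective stated as number.

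Finally, moving to counts may not be free. If the 5% placebo rate belongs to Treg% and independent lymphocyte variation adds a log-SD of 0.10, 0.15 or 0.20 (assumed values), the placebo rate on counts becomes about 8, 12 or 15%. The same formula, with 50% response on drug, then needs about 22, 27 or 34 per arm in place of 18. The direction is plausible; the sizes are assumptions.

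**Conclusion.** The point holds as an unresolved contradiction about the primary variable. The objective and outcome are on number, the one responder definition with a named scale is on proportion, and the analysis section names no scale and uses a slightly different threshold. The 23.1% figure is exact if Treg% of total lymphocytes governs and the Treg count is unchanged. The responder rates of 27, 40 and 56% are illustrations that rest on the assumed falls, a common fall in all treated patients, log-normality and a log-SD taken from a planning ceiling.

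The stronger conclusion, that the trial would declare its aim met with no rise in Tregs, is not supported. It needs both the proportion reading and a selective lymphocyte fall, and the protocol establishes neither. The sample size of 54, then 63, is not shown to be wrong. The correction still matters, because the ambiguity bears on the trial's main conclusion and can be removed before the data are seen.

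**What to change.** - Define the responder in 2.13 and 2.14 on absolute Treg count (cells/µL), to match 2.1 and 2.9.
- Use one threshold throughout, either ≥30% or >30%.
- Report Treg%, with its parent population named, and total lymphocytes as supporting variables.
- State that a rise in Treg% alone will not be reported as an increase in Treg number.

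The text change is small. Two checks go with it. Absolute counts may vary more within patients, so the assumed 5% placebo response rate should be reconsidered on that scale and, if it rises, the power at 18 evaluable patients per arm recalculated. A lymphocyte count is on the haematology panel in 2.11, but the visit table is not shown, so it should be confirmed that one is taken with the baseline and week-18 Treg samples.
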